## **I. Efficacy and Safety Evaluations**

Please see the information following the table in III.A. above for the timing of outcome measures. These fall into the following categories:

### **Primary and Secondary Efficacy Measures**

Primary: blinded BPRS ratings of psychosis; Clinical Global Impression/Improvement scores

Secondary: PDQ-39 quality of life scores, ADL assessments (Schwab-England, UPDRS), sleep log, and Beck depression rating scales

### **1.2. Safety and Safety Monitoring**

The primary safety measures will be UPDRS motor ratings, sleep log, and MMSE, in addition to a clinical Review of Systems on each visit. The Review of Systems is integrated into our routine patient care database. Significant **adverse events** will be reported to Lilly on standard forms. No routine clinical laboratory tests are anticipated.

### **3. Drug Accountability**

A pill count will be performed on each Week 2 or Week 4 visit. Records will be kept for each patient of total pills used.

## **IV. Data Analysis Methods (including any interim analyses)**

The 0-2 week and 2-4 week periods will be treated as two separate study periods for the purpose of statistical analysis, due to the possible addition of dopamimetics at the 2-week visit; the change from 0 to 2 weeks will be the primary test of efficacy. If we have few dropouts, a repeated-measures ANOVA with post-hoc tests would be adequate and powerful (dependent variable: BPRS positive symptom subscale scores; grouping variable: dose; within variable: time). Otherwise a more complicated actuarial analysis might be needed. We have collaborated in the past with the biostatistics group here at Washington University. Investigators will remain blinded throughout accrual and treatment. See section III.D.2. above for a preliminary analysis of data, after treatment of 30 subjects, by a statistical consultant not otherwise participating in the study.

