## **II. Objectives**

### Primary

- 1) Determine whether olanzapine has superior efficacy to placebo in treating psychosis in patients with Parkinson's disease (PD) who are being treated with dopaminergics.
- 2) Determine whether in this setting a daily (qhs) dose of 10mg is more effective than a daily dose of 5mg.

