## **III. Investigational Plan**

### **A. Summary of Study Design**

Patients will be screened and if they meet the criteria given in section III.D.1. will enter into one of three arms, shown as three rows of the table below. Each arm will consist of nightly

(qhs) dosing of matched tablets or capsules containing 0, 5, or 10 mg of olanzapine. However, patients in the 10 mg arm will take only 5 mg nightly for the first week.

See the table below for a diagrammatic summary of the study design.

| baseline                          | 1st week | 2nd week | 2-wk visit                                                      | weeks 3-4 | 4-wk visit                                                 |
|-----------------------------------|----------|----------|-----------------------------------------------------------------|-----------|------------------------------------------------------------|
| clinical evaluation;
randomize | placebo  | placebo  | clinical evaluation;
increase
dopamimetic if
indicated | placebo   | clinical evaluation;
return to routine
clinical care |
|                                   | 5mg      | 5mg      |                                                                 | 5mg       |                                                            |
|                                   | 5mg      | 10mg     |                                                                 | 10mg      |                                                            |

Baseline evaluation:

Psychiatric, neurologic and general medical history and examination; Clinical Global Impression (CGI) by MD, PDQ39 (a brief, self-rated overall quality of life questionnaire), videotaped psychiatric interview for later blinded BPRS (Brief Psychiatric Rating Scale) rating, Schwab-England ADL assessment, full UPDRS (Unified Parkinson's Disease Rating Scale), MMSE (Folstein Mini-Mental State Examination), HDRS (Hamilton Depression Rating Scale), Beck depression inventory (Beck), patient- or caretaker-reported sleep hours/quality

Interim evaluation:

clinical evaluation; CGI (MD, pt, caretaker), videotaped psychiatric interview for later blinded BPRS, Schwab-England, full UPDRS, MMSE, pill counts, PDQ39, Beck, sleep hours

Final evaluation:

clinical evaluation; CGI (MD, pt, caretaker), videotaped psychiatric interview for later blinded BPRS, Schwab-England, full UPDRS, MMSE, pill counts, PDQ39, Beck, sleep hours

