**B. Rationale for Design and Control**

Our design can significantly strengthen the conclusions of Wolters et al. (1996) in three ways. First, with the parallel group, placebo-controlled design, we can show whether olanzapine is superior to placebo in treating PD psychosis. Second, with a fixed dose design we can address the question of optimal olanzapine dose in these patients. Third, the Wolters et al study did not use blinded ratings of psychosis. To address this, we will videotape clinical interviews at each study visit. The main outcome measure, BPRS ratings of psychosis, can then be rated after the end of the study by an investigator who will be blind not only to olanzapine dose but also to duration of treatment (0, 2, or 4 weeks). This will allow us to show that improvement in any treatment group is not due to investigator or patient expectation of improvement, and may also increase our power as the placebo group may show less change.

We chose 4 weeks rather than a longer study period because clinical experience and the Wolters et al. trial both suggest that improvement in psychosis is usually seen by this point.

The doses chosen are due in part to the desire to bracket the mean final dose in the open study (7mg/day), and in part to the fact that olanzapine is marketed in 5mg and 10mg tablets.

A placebo control is not only scientifically needed but also ethically justified, given the potential side effects of either olanzapine or other treatments of psychosis in this population (beyond the conservative measures we require for study entry).

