#### **F. Dosage and Administration**

See the summary table in III.A. for an overview. Patients who meet entry criteria will take identical study tablets nightly, containing either 5mg or 10mg olanzapine or placebo. Due to concerns about the tolerability of starting olanzapine abruptly at the 10mg qhs dose, we plan to administer only 5mg nightly for the first week of the “10mg” arm.

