##### **1. Materials and Supplies**

We will use matching dose cards, one for each week of the study, each with 9 days’ supply of drug. The last 2 days will be clearly marked as extras, and will be used to better assess compliance and in the event that a patient is a day or two late returning to clinic. Each card will be marked “Week 1”, “Week 2”, etc., as appropriate. Each card will also be marked with a code (e.g. A, B, or C) which will indicate which study arm is involved. Here, “A”, “B”, and “C” refer to the placebo, 5mg, and 10mg arms, but of course not necessarily in that order. We will also ask Lilly to supply us simultaneously with a sealed envelope containing the code, *e.g.* A=placebo, etc. This envelope will remain sealed until 30 patients have been enrolled, as described above.

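### The primary 0–2 week test compares the active arms after only 7 of 14 nights on different doses, so it cannot by itself answer the 10 mg versus 5 mg objective

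*Protocol*

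**What the plan says.** The second of the two primary objectives (Protocol, II. Objectives, Primary) is: "Determine whether in this setting a daily (qhs) dose of 10mg is more effective than a daily dose of 5mg". Section III.B presents the design as able to settle this: "with a fixed dose design we can address the question of optimal olanzapine dose in these patients".

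The dosing sections state that the upper arm does not start at its nominal dose. Section III.A says that "patients in the 10 mg arm will take only 5 mg nightly for the first week", and its table shows the same step. Section III.F repeats it ("we plan to administer only 5mg nightly for the first week") and gives tolerability as the reason.

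Section IV splits the trial into a 0–2 week and a 2–4 week period, "due to the possible addition of dopamimetics at the 2-week visit", and then fixes the primary window: "the change from 0 to 2 weeks will be the primary test of efficacy". The proposed analysis is a repeated-measures ANOVA of the BPRS positive symptom subscale, grouped by dose, with post-hoc tests. No other window is given for the dose objective, and the shared first week is not mentioned where the analysis is described.

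**The concern.** One primary test is made to serve two primary objectives, and it suits them unequally. Against placebo, both active arms have had 14 nights of olanzapine by week 2. Between the active arms, the regimens are identical until night 8, so any advantage of the higher dose has one week in which to appear.

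If the plan is followed as written, the week-2 contrast of the active arms will be reported as the answer on daily 10 mg versus daily 5 mg. In fact it compares one week of 5 mg followed by one week of 10 mg with two weeks of 5 mg. The main risk is a null result. It could be taken to mean that the higher dose adds nothing, when the trial had not compared the two daily doses over the whole primary window.

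**Working it through.** **Inputs.** Primary window: 0–2 weeks, nominally 14 nights (section IV). Upper arm: 5 mg nightly in week 1, then 10 mg (III.A, III.F). Lower arm: 5 mg throughout (III.A). Each weekly card is supplied "each with 9 days’ supply of drug", the last two days being spares (III.F.1). Sample size: 10 per arm, possibly 15 (III.D.2).

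**Exposure.** Differing nights = nights to the visit − 7. Mean nightly dose in the upper arm = (7 × 5 + differing nights × 10) / nights to the visit.

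| Visit | Differing nights | Upper arm mean | Lower arm mean | Separation | Share of nominal 5 mg |
|---|---|---|---|---|---|
| Week 2 | 14 − 7 = 7 | (35 + 70)/14 = 7.5 mg | 5 mg | 2.5 mg | 50% |
| Week 4 | 28 − 7 = 21 | (35 + 210)/28 = 8.75 mg | 5 mg | 3.75 mg | 75% |

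If the week-2 visit is one or two days late and the spare doses are taken at the week-2 dose, the differing nights are 15 − 7 = 8 or 16 − 7 = 9.

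**The plan's own power figure.** Section III.D.2 states 90% power for a 50% improvement in total BPRS within one group of 10–11 patients. It gives no mean or SD, and it says that the variance of change is not available, so the figure cannot be reproduced. Solving backwards with a two-sided paired t test at 0.05, 90% power implies a standardised within-group change of about 1.15 (n = 10) or 1.09 (n = 11). No power is stated for 10 mg versus 5 mg.

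**Illustration only.** Three things are assumed, none of them from the protocol:
- the standardised effect of 10 mg over placebo, d, lies between 1.087 and 1.534;
- 5 mg is half as effective as 10 mg, so the undiluted 10 versus 5 difference is d/2;
- the difference expressed at a visit is proportional to the mean-dose separation up to that visit.

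The lower value of d borrows the within-group effect at n = 11. The upper value is simply the between-arm effect that would give 90% power at 10 per arm, which the protocol never claims. Two-sample t test, two-sided 0.05:

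| Comparison | Standardised difference | Power, 10 per arm | Power, 15 per arm |
|---|---|---|---|
| Week 2 (50% share) | 0.50 × d/2 = 0.27 to 0.38 | 9–13% | 11–17% |
| Week 4 (75% share) | 0.75 × d/2 = 0.41 to 0.58 | 14–23% | 19–33% |

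Week 4 is the fair comparator because neither visit offers full separation. Under these assumptions it helps, but the dose contrast stays weak at either visit.

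**Does the planned 2–4 week analysis fill the gap?** No. Change over 0–4 weeks = change over 0–2 weeks + change over 2–4 weeks. Taking weeks 2–4 as a separate period removes whatever difference the arms built up in week 2, so it does not estimate the 0–4 week dose contrast.

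**The case against.** Week 2 is a reasoned choice. Dopamimetics may be raised at that visit, and section III.H otherwise tries to hold CNS-active doses steady, so the 0–2 week change is the cleaner comparison. A week-4 contrast takes in that post-randomisation change. If patients who respond better are titrated up more, the arms are pulled together, which is again a bias towards no difference. This stands, and it is why week 4 is not put forward as the one correct primary window.

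The week-1 step is disclosed, and week-4 BPRS interviews are taped, so no data are lost. This also stands, but it does not change which test is primary or what that test can conclude.

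Three stronger readings are tempting and are not supported:

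- A reader might infer that the dose effect is halved and that four times as many patients are needed. That requires response to follow mean nightly dose. The BPRS is rated from an interview held after a week at the full 5 mg separation. If response followed current dose without lag, dilution would be small.
- A reader might infer that the window alone ruins the power of the dose comparison. Under the illustrative model, power is low at week 4 too, so most of the shortfall is sample size, which is a separate matter.
- A reader might infer that section III.B contradicts a week-2 test by saying of four weeks that "improvement in psychosis is usually seen by this point". That sentence explains why the study is not longer. It does not say that improvement is absent at two weeks. Equally, the protocol offers no statement that two weeks is enough.

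**Conclusion.** The point holds as a mismatch between an objective and its test. The only primary efficacy test compares the active arms when they have differed on 7 of 14 nights (8–9 with a late visit), at half the nominal mean-dose separation. This follows from the objectives, the dosing table and section IV, and rests on no effect-size assumption. It means that a null week-2 result cannot support a conclusion of no difference between daily 10 mg and daily 5 mg. The comparison with placebo is much less affected.

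Section IV does not say in words that the 0–2 week test also answers objective 2. But it is the only primary efficacy test defined, and its grouping variable is dose.

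The amount of dilution is unknown. The power figures above depend on assumptions and should not carry the conclusion.

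**What to change.** Reconcile objective 2, the week-1 dosing and the primary window in the protocol text before the treatment code is opened:

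1. Keep the 0–2 week change as the primary test of olanzapine versus placebo.
2. State that the week-2 contrast of the active arms compares two regimens as given over two weeks (5 mg for one week then 10 mg, versus 5 mg throughout), and limit the objective 2 conclusion to that.
3. Add a comparison of the active arms on the week-4 BPRS positive-item score, adjusted for the week-0 score, by assigned arm in all randomised patients, whether or not dopamimetics were raised at week 2. Report dopamimetic increases by arm beside it.

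The cost is wording and one further analysis, since the week-4 tapes are already planned. The downside is that the week-4 contrast includes any effect of the dopamimetic increases, which may pull the arms together. Whether to make it the primary test of objective 2 is therefore for the sponsor to decide and to record in advance. No change to dosing is proposed.

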## **V. Informed Consent, Ethical Review, and Regulatory Considerations**

See attached documents submitted to the Washington University School of Medicine Human Studies Committee.

Since olanzapine has an FDA indication for treatment of “psychotic disorders,” the use of olanzapine to treat psychosis in this trial is considered to be within the scope of the current labeling. Also, given the positive tolerability data from the open study in PD, (Wolters et al., 1996), we do not feel that use of olanzapine in this population constitutes any additional risk.

However, since it is possible that data from this study may eventually be used to support a request to the FDA for a change in labeling or advertising for olanzapine, we are applying to the FDA for an Independent IND approval.

